### Sample size and randomization

Households will be randomly allocated to a study arm at a ratio of 1:1. A randomization list was generated by an independent statistician with a block size of 4. Sealed and consecutively numbered envelopes containing treatment assignment and study documents are provided to the study nurses. It was not possible for treatment to be blinded.

The sample size for this trial is based on the primary endpoint of linkage to care within 3 months after HIV diagnosis. We expect 3-month linkage to care rates of 40 % in the control and 60 % in the intervention arm. As the trial is randomized at the household level, we require a total of 260 households with at least one HIV-positive participant to detect a 20 % increase in linkage to care assuming a Type I error rate of 5 % and power of 90 %. With an estimated uptake of HTC of 94 %, a prevalence of previously untreated HIV infection during home-based HTC campaigns of 5 %, and a 10 % trial participation refusal rate or choice of alternative health facility, we need to visit 6200 households to achieve the desired sample size of 260 households. In case more than one HIV-positive individual is diagnosed in the household, all individuals meeting eligibility criteria will be included and randomized to the same arm. This will only serve to increase the power of the study.

With the proposed sample size above, we will have sufficient power to test the second primary endpoint of viral suppression at 12 months. As those not linking to care will be considered as failures, we expect viral suppression rates of 25 % in the control arm and 45 % in the intervention arm. With 130 individuals per arm, we will have 93 % power to detect a difference of 20 % in viral suppression rates.

Analysis will be as intention to treat. The study will be analysed using mixed effects logistic regression models in order to account for the clustering of households (if sufficient number of households include more than one HIV-positive individual in the study) and village. If the arms are not found to be balanced on important risk factors for linkage to care and viral suppression, these risk factors will be adjusted for in models. Linkage and viral suppression rates between the control and intervention arm will be presented with odds ratios and 95 % confidence intervals.

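### Household, the randomised unit, enters the primary model only under an undefined condition; household-robust inference should be used whatever the number of multi-participant households (low to moderate severity)

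*Protocol article*

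**What the plan says.** All of this is in the protocol article, *Sample size and randomization*.

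- Unit of randomisation: "Households will be randomly allocated to a study arm at a ratio of 1:1". Where a household has several HIV-positive people, "all individuals meeting eligibility criteria will be included and randomized to the same arm".
- Model: "The study will be analysed using mixed effects logistic regression models". It is to account for "clustering of households (if sufficient number of households include more than one HIV-positive individual in the study"), and for village. Village is therefore always in the model and household only conditionally.
- Reporting: the comparison between arms "will be presented with odds ratios and 95 % confidence intervals". The text does not say whether the odds ratio is conditional on household and village or marginal.
- Planning effect: "We expect 3-month linkage to care rates of 40 % in the control and 60 % in the intervention arm". These are marginal proportions.

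The section gives no number that would count as sufficient, no method for the case where the household term is omitted, no expected share of multi-participant households and no intra-household correlation.

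**The concern.** Members of one household receive the same allocation. They also share influences on linkage, such as distance to the clinic. The analysis has to respect that whatever the number of such households. The stated rule allows two different analyses of both primary outcomes, and each has a weakness.

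- **Household omitted.** Members of one household are treated as independent, and standard errors are too small. The village term does not fully repair this, because households are nested in villages and their members can be more alike than neighbours are.
- **Household kept, most households having one participant.** A single binary outcome per household carries almost no information on household variance, so the few multi-participant households determine it. In a logistic random-intercept model that variance also scales the treatment odds ratio. A poorly estimated nuisance parameter then moves the headline result.

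At stake are slightly optimistic confidence intervals in one branch. In the other, the odds ratio is unstable and is not on the scale of the effect used to size the trial.

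**Working it through.** **Inputs from the document:** randomisation by household; 40% versus 60% linkage; 25% versus 45% viral suppression; type I error 5%; power 90%; 260 households; 130 individuals per arm and 93% power for viral suppression.

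**Assumed, because the document gives neither:** f, the share of enrolled households with two participants (the rest have one), and ρ, the within-household correlation left after village is accounted for. For the random-effect model, the latent-scale correlation (ICC) is assumed.

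**1. Reproducing the plan's figures.** Two-sided, pooled variance, no continuity correction:

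n per arm = [1.960·√(2·0.5·0.5) + 1.282·√(0.4·0.6 + 0.6·0.4)]² / 0.20² = [1.386 + 0.888]² / 0.04 ≈ 129.3, so 130 per arm and 260 in total.

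For 25% versus 45% with 130 per arm, power is 92.7% (93.3% unpooled), against the stated 93%. Both figures reproduce with one participant per household.

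**2. Household term omitted.** With household sizes 1 and 2, Σm²/Σm − 1 = 2f/(1+f), so the design effect is DE = 1 + 2fρ/(1+f). A nominal 5% test has actual type I error 2·[1 − Φ(1.96/√DE)]. Example: f = 10%, ρ = 0.5 gives DE = 1 + 0.10/1.10 = 1.091, √DE = 1.044, and type I error 6.1%.

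| f | ρ | DE | SE too small by factor | Type I error |
|---|---|---|---|---|
| 2% | 0.3 | 1.012 | 1.006 | 5.1% |
| 2% | 0.5 | 1.020 | 1.010 | 5.2% |
| 5% | 0.3 | 1.029 | 1.014 | 5.3% |
| 5% | 0.5 | 1.048 | 1.024 | 5.6% |
| 10% | 0.3 | 1.055 | 1.027 | 5.6% |
| 10% | 0.5 | 1.091 | 1.044 | 6.1% |
| 20% | 0.3 | 1.100 | 1.049 | 6.2% |
| 20% | 0.5 | 1.167 | 1.080 | 7.0% |

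**3. Household term kept: what the odds ratio measures.** The planned marginal odds ratio is (0.60/0.40)/(0.40/0.60) = 2.25 for linkage and (0.45/0.55)/(0.25/0.75) = 2.45 for viral suppression. For the household-conditional value, set σ² = (π²/3)·ICC/(1 − ICC). Then find the intercept in each arm at which the logistic curve, averaged over a normal household effect with SD σ, returns the planned proportion.

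| Latent ICC | σ | Conditional OR, 40% v 60% | Conditional OR, 25% v 45% |
|---|---|---|---|
| 0.1 | 0.60 | 2.41 | 2.63 |
| 0.3 | 1.19 | 2.82 | 3.11 |
| 0.5 | 1.81 | 3.53 | 3.95 |

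**4. Household term kept: how well it is estimated.** 300 simulated trials per row, 260 households, latent ICC 0.3, true conditional OR 2.82, maximum-likelihood random-intercept logistic model, no village effect. The pooled OR ignores household and targets the marginal 2.25.

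| f | Household variance estimated at about zero | Random-effect OR, median (5th–95th percentile) | Pooled OR, median (5th–95th percentile) |
|---|---|---|---|
| 5% | 25% of trials | 2.99 (1.64–13.69) | 2.31 (1.56–3.48) |
| 10% | 16% | 3.01 (1.71–9.50) | 2.29 (1.53–3.46) |
| 20% | 6% | 2.83 (1.61–6.21) | 2.24 (1.51–3.38) |

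The medians lie close to their targets, so the problem is spread. At f = 5% the 95th percentile is 13.69/1.64 = 8.3 times the 5th, against 3.48/1.56 = 2.2 times for the pooled OR. At f = 20% the ratios are 3.9 and 2.2.

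**The case against.** **The rule limits its own harm.** The household term is dropped only when few households have several participants, which is when ignoring it costs least, and the condition guards against fitting a variance that cannot be estimated. This stands for the standard errors: a type I error near 7% requires someone to judge 20% two-person households insufficient. It stands less well for the other branch, because sufficient is undefined and the random-effect odds ratio is still widely spread at 10–20% pairs.

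**The document's planning figures point to few pairs.** Viral suppression is powered on 130 individuals per arm, *Nested studies* gives 260 HIV-positive participants against 260 households, and 6200 × 0.94 × 0.05 × 0.90 = 262 is about one participant per enrolled household. These do not exclude pairs, but they favour the upper rows of the type I error table.

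**Details may sit in the SAP.** A threshold could be set there. The protocol article does not simply leave the matter open, however: it states a rule under which the randomised unit may be left out.

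A reader might infer three stronger claims that the document does not support:

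- *The branch is chosen from the results.* The trigger is the number of multi-participant households, which is fixed at enrolment and is not an outcome.
- *The conditional odds ratio is biased or inflated.* It is a different estimand. The objection is to its instability and to its mismatch with the planned contrast.
- *The remark on extra members, "This will only serve to increase the power of the study", is wrong.* With equally weighted individuals, information per household falls below one person's worth once ρ exceeds (1+f)/2; at f = 10%, ρ = 0.7 it is 1.10/(1 + 0.14/1.10) = 0.976. The planned model is a mixed model, which approximates efficient weighting. A pair then carries 2/(1+ρ), never below 1, and the same case gives 0.90 + 0.10 × 2/1.7 = 1.018. For the planned analysis the remark is not shown to be wrong, and it is not part of this point.

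**Conclusion.** The point holds at low to moderate severity. The protocol randomises households but makes accounting for them depend on an undefined condition, with no fallback. If household is omitted, the loss of type I error control is small: about 5.1–5.6% at 2–5% two-person households and 5.6–6.1% at 10%, both for ρ of 0.3–0.5, and up to about 7% at 20% with ρ = 0.5. If household is kept with few pairs, the consequence is more visible: a poorly identified variance and an unstable household-conditional odds ratio, centred between 2.41 and 3.53 for latent ICC 0.1–0.5 where the planned marginal value is 2.25.

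These sizes rest on assumed f, ρ and ICC, on households of one or two participants, and on simulations without a village effect. The conclusion that the rule should not be conditional does not depend on them. The 260 households are unaffected.

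**What to change.** Delete the parenthesis. For both primary outcomes, always base primary inference on household-cluster-robust standard errors. Use logistic GEE with an independence working correlation, or logistic regression with household-clustered variance; single-participant households are clusters of one, so no threshold is needed. Report the marginal odds ratio with the marginal risk difference beside it, since the trial is sized on a 20-point difference. Keep the household random-effect model as a sensitivity analysis and label its odds ratio as conditional.

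Continue to account for village, and state how. One indicator per village could be too sparse: 6200 households at 40–80 per eligible rural village would be about 78–155 villages for 260 enrolled households, ignoring the urban neighbourhoods. Facility as a covariate or stratum is one alternative.

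The cost is a wording change. Confidence intervals become slightly wider if pairs exist. Independence weighting also gives up a little efficiency when correlation is high. At f = 10%, effective size per arm is 143/1.091 = 131.1 at ρ = 0.5 (power 90.4%) and 143/1.145 ≈ 124.8 at ρ = 0.8 (power 89.0%). That is a small price for an analysis that is valid for any number of multi-participant households.

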### Control and intervention arms

The control group follows the standard of care in Lesotho [35, 36] that is similar to most settings in Sub Saharan Africa. During the household visit, individuals found HIV-positive and randomized to the control arm will receive post-test counselling and a referral letter with an appointment at their chosen health facility. On the first visit to the clinic, the participant receives a laboratory assessment (CD4 cell-count, serum creatinine, haemoglobin) and a first adherence counselling session. The participant must then return to the clinic to receive his/her laboratory results and to undergo a second adherence counselling session. Depending on whether the participant is judged as “ready to start ART” by the counsellor at the clinic, he/she may start ART at their second clinic visit or have to attend a third adherence counselling session. Once the participant has started ART, the first and second follow-up visits are scheduled for 14 and 28 days after ART initiation, respectively. Thereafter, follow-up visits are scheduled monthly until 6 months after ART initiation. If the participant is clinically stable, clinical follow-up visits may then be spaced to 3-monthly intervals, but refills of ART must still be collected on a monthly basis.

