Participants randomized to the intervention group receive post-test counselling and clinical and laboratory assessment with the possibility of same day ART start combined with a reduced frequency of follow-up visits. Directly after the positive HIV-test result the study nurse assesses the participant clinically and performs point-of-care laboratory testing (serum creatinine (StatSensor Creat®, Nova® Biomedical), haemoglobin (Hemocue®, HB301), and CD4 cell-count (PIMA Alere®)). Thereafter, the participant receives a standardized short adherence counselling. After adherence counselling, if – according to the nurse’s judgement - the person understood the implications of lifelong ART, he/she will be offered to start ART immediately. Those who decide to start ART during the visit or intend to start within 7 days will receive a 30-day ART-supply and a follow-up appointment at the clinic within 12 to 16 days. Choice of ART regimen and use of cotrimoxazole prophylaxis follows national and international guidelines [36, 37]. Participants with a CD4 cell-count < 100 cells/mL will receive testing for cryptococcal antigen. In case of a positive result, the participant will be treated according to guidelines and excluded from the study. In order to reduce travel time and transport cost, participants who are clinically stable, will have their follow-up visits and ART refills more widely spaced with appointments at 6 weeks, 3, 6, (9) and 12 months after ART initiation. Participants are, however, encouraged to visit the clinic at any time in case of problems or questions.

Figure 1 summarizes flow of participants in the study.

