**Table Taba:** 

Service provided	Control group	Intervention group
Baseline laboratory values (creatinine, CD4-count, haemoglobin)	Blood taken at first clinic visit after the positive HIV test result, results communicated at second clinic visit.	Performed in the community the day of the HIV test result as point-of-care
Adherence-counselling	At first and second clinic visit	In the community, directly after the HIV test result
ART-initiation	After at least two adherence counselling sessions at the clinic	Proposition of starting the same day as tested HIV positive
Follow-up visits and drug-refills at the clinic	Monthly	2 weeks – 6 weeks – 3–6–9–12 months

Table 1 Overview of services provided after a positive HIV test result during community-based HTC campaigns in the control and intervention group

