### Subgroup analyses

Individuals working outside of Lesotho (primarily in South Africa) are considered as a special subgroup as they usually spend several months out of the country at a time. This makes them an especially challenging group to link to care, but once linked, they are typically given refills and appointments every 3 months to accommodate their work schedule. Rather than exclude these individuals, we assume they will be evenly distributed among the treatment arms and they will be analysed in a separate subgroup analysis. As this group has rarely been studied, we do not have valid estimates of their expected linkage to care or viral suppression rates. In addition, we do not expect to have the power to sufficiently test for differences among these groups but nevertheless find their results of great interest for the design of future interventions targeting this difficult-to-treat population.

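### Covariates enter the primary models only if the arms look unbalanced; a fixed set is better, and it should exclude laboratory values that controls first have measured at the clinic

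*Protocol article*

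**What the plan says.** The rule is in the Protocol article, Sample size and randomization: "If the arms are not found to be balanced on important risk factors for linkage to care and viral suppression", those factors are adjusted for in the mixed effects logistic models. No factor and no criterion for imbalance is given. The same paragraph commits to intention to treat and to accounting for clustering by household (if enough households contribute more than one participant) and by village.

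The timing of the laboratory values is in Control and intervention arms.
- **Controls** are allocated at home: "During the household visit, individuals found HIV-positive and randomized to the control arm will receive post-test counselling and a referral letter". Their tests come later: "On the first visit to the clinic, the participant receives a laboratory assessment (CD4 cell-count, serum creatinine, haemoglobin". The table comparing services in the two arms agrees: "Blood taken at first clinic visit after the positive HIV test result, results communicated at second clinic visit".
- **Intervention participants** are also tested after allocation, but on the same day: "Participants randomized to the intervention group receive post-test counselling and clinical and laboratory assessment", and in the table "Performed in the community the day of the HIV test result as point-of-care".

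That table labels creatinine, CD4 count and haemoglobin as baseline values. Primary outcomes defines linkage as at least one clinic attendance within 90 days of enrolment. Subgroup analyses says of people working outside Lesotho: "This makes them an especially challenging group to link to care". It assumes that they will be evenly spread over the arms.

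**The concern.** There are two linked problems.

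**The trigger.** Choosing covariates by observed balance makes the primary model depend on the data. It also misses the main reason to adjust in a randomised trial: a covariate that predicts the outcome improves precision whether or not it is balanced. By the article's own account, working outside Lesotho is such a factor, yet it would enter the model only if the arms happened to differ on it.

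**What the trigger could select.** CD4 count and haemoglobin are natural candidates as risk factors for viral suppression, and the article calls them baseline values. In the control arm, however, they exist only for people who attended the clinic. A balance check on them would compare all intervention participants with control attenders only, so selection alone could look like imbalance and prompt adjustment. Adjusting with missing cases dropped would then remove control failures from both primary comparisons.

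**Working it through.** **1. The plan's own figures.** Inputs from Sample size and randomization: linkage 40% v 60%, 5% type I error (taken as two-sided), 90% power, 1:1 allocation. With pooled variance under the null:

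n per arm = [1.96·√(2·0.5·0.5) + 1.2816·√(0.4·0.6 + 0.6·0.4)]² / 0.20² = (1.386 + 0.888)² / 0.04 ≈ 129.3, so 130 per arm and 260 in total. This matches the plan.

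For viral suppression at 25% v 45% with 130 per arm: z = [0.20·√130 − 1.96·√(2·0.35·0.65)] / √(0.1875 + 0.2475) = (2.280 − 1.322)/0.660 ≈ 1.45, giving power of 92.7%. This matches the stated 93%. The sample size is not in question.

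**2. Cost of the conditional rule alone.** Simulation of 260 independent participants, 3,000 runs. Assumptions: one covariate measured in everyone, odds ratio 2 per standard deviation; control log-odds set at 0.4/0.6; treatment odds ratio 1 or 2.25; imbalance judged by a two-sided 5% test. That test is an assumption, as the article gives no criterion.

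| Analysis | Type I error | Power |
|---|---|---|
| Unadjusted | 4.8% | 84.1% |
| Adjusted only if unbalanced | 4.6% | 84.4% |
| Always adjusted | 4.4% | 86.4% |

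The simulation standard error of a 5% rate is √(0.05·0.95/3000) ≈ 0.4 points, so the type I error figures are not distinguishable from 5%. Under the alternative, the rule triggered adjustment in 5.3% of runs, so it behaves almost like no adjustment. The loss is 86.4 − 84.4 = 2.0 points of power.

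**3. Who would have laboratory values.** Intervention arm: all 130 by design. Control arm at 90 days: 0.40 × 130 = 52, so 130 − 52 = 78 (60%) lack them. The Background reports 25% linkage at one month in an earlier Lesotho trial and rates mostly below 50% elsewhere. The number lacking values would be 130 × 0.75 ≈ 98 at 25% linkage and 130 × 0.50 = 65 at 50%.

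**4. If those values were used and missing cases dropped.**
- *Linkage.* With no late attenders, the retained controls are 52 of 52 linked (100% v 60%, instead of 40% v 60%). If L controls first attend after day 90, they have values but are not linked, and the retained rate is 52/(52 + L). It falls below 60% only when L exceeds 52/0.60 − 52 = 34.7, that is, when at least 35 of the 78 attend late.
- *Viral suppression.* Suppressed controls number 0.25 × 130 = 32.5. If all of them have values, the retained rate is 32.5/(52 + L). With L = 0 it is 62.5%, and the crude odds ratio moves from (0.45/0.55)/(0.25/0.75) = 2.45 to (0.45/0.55)/(0.625/0.375) = 0.49. The direction stays reversed until L exceeds 32.5/0.45 − 52 = 20.2.

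**The case against.** The strongest reply is that the article never names CD4 count, haemoglobin or creatinine as adjustment variables. They appear as services and, for CD4 count and haemoglobin, as secondary change outcomes. The covariate list may sit in a document not shown. The article commits to intention to treat and counts those not linking as failures for viral suppression; a model that dropped 78 controls would contradict both. An analyst who saw 60% of one arm missing would probably stop. All of this stands: the harm in step 4 needs two choices, picking these values and deleting missing cases, and the article states neither.

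The absence of values in non-attenders is also inferred. Storage of plasma provides for samples at recruitment, and Nested studies plans lipid and HbA1c measurements in consenting trial participants, so some research blood is taken outside routine services. But the stored plasma is for resistance testing, and no section gives a CD4 count, haemoglobin or creatinine for a control who never attends.

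Finally, the conditional rule on its own does little damage, as step 2 shows. A reader might infer that it inflates type I error or undermines the p-value; the simulation does not support that.

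What survives is that the imbalance trigger is a stated rule. A covariate list elsewhere would narrow it but not remove it.

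**Conclusion.** The point holds in a limited form. Adjusting only for factors found unbalanced is an inferior rule: the model depends on the data and about 2 points of power are given up. The 2 points rest on the assumed covariate strength, a single covariate, an assumed 5% balance test and independent participants.

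The warning about laboratory values is conditional. If they were used with missing cases dropped, about 78 of 130 controls would leave the model at the planned linkage rate, and both comparisons could reverse. A reader might infer that the plan as written destroys the linkage comparison, or that having these values is identical to having linked. The article supports neither: it does not select these covariates, and a control first attending after day 90 has values without counting as linked, so the overlap is close but not exact. It is still close enough to justify ruling these variables out explicitly.

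**What to change.** Replace the conditional sentence with a fixed covariate set for both primary models, used whatever the observed balance and limited to items recorded at the household visit in both arms: age, sex and working outside Lesotho. Add facility catchment only if the village effect does not already cover it; Recruitment and participants confines each eligible rural village to one catchment, so it largely may. State that laboratory values first measured at the clinic in controls (CD4 count, haemoglobin, creatinine) are used neither as covariates nor for balance checks in the primary models. Report the unadjusted result as a sensitivity analysis.

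The cost is a change of wording and a few extra model parameters; the sample size stays at 260 households. It assumes that work location is recorded at enrolment. The planned subgroup analysis implies this, but the article does not list the contents of the enrolment form, so it should be confirmed.
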